### 2.6. Sample Size Calculation

The sample size was estimated based on the primary endpoint of MVPA time per week. After the program, a mean difference in MVPA of 30 (SD = 60) minutes per week between the intervention and the control groups was expected based on existing evidence from physical activity intervention studies (alpha = 0.05 and 80% power) [30]. To detect this effect, a sample of *n* = 64 per group is needed. Assuming a drop-out rate of 20%, this yields a sample size of *n* = 80 per group and *n* = 160 participants in total.

### 2.7. Recruitment

Participants who reside in the northern part of Singapore were recruited from KTPH and NUS by trained members of the study team at the respective sites and via letters plus phone calls to a list of past screening participants. Recruitment occurred between April and December 2016. Although the study used additional recruitment mechanisms, approximately 90% of the participants were recruited from the KTPH Community Screening program which is described in detail below. Only 6 participants were recruited by calling 154 participants in an NUS cohort from a list of 307 and an additional 9 were recruited via opportunistic screening mechanisms (e.g., at ad-hoc events). The participant flow is shown in Figure 1.

To increase overall attendance of the health screenings, the study team, research collaborators and persons authorized by the research team promoted the screenings by mechanisms including hanging up posters and handing out flyers in their divisions/departments but also at public venues such as MRT stations. In addition, flyers were distributed and there were ad hoc events where promotion of the screenings also occurred. The screenings were also advertised on relevant NUS and research collaborator websites and Facebook pages. The participants were reimbursed SGD$20 at baseline and SGD$30 after study completion for their time.

#### 2.7.1. Main Recruitment Mechanism: KTPH Community Screening Program

On community health screening days, participants were directed to the NUS PPT booth upon completing their health screening. The NUS team briefly explained the study, administered the PAR-Q2 and handed out the Participant Information Sheet to those who expressed interest and were deemed safe to participate in physical activity after completing the PAR-Q2. Potential participants were informed that activities at the PPT booth occurred for research purposes and that they were not part of the health screening. They were also informed that completion of the PAR-Q2 was voluntary and that completion of the PAR-Q2 did not mean they had to participate in the research. A unique study ID was noted on each PAR-Q2 form. Participants’ National Registration Identity Card (NRIC) number was noted on a separate sheet, listed after their respective study ID. A list containing the NRIC numbers of those who passed the PAR-Q2 was handed to the KTPH health screening team. Subsequently, a study nurse checked participants’ blood pressure values and fasting glucose levels obtained from the health screening. Those who met the selection criteria were shortlisted for the study.

During the following days, eligible people received a text message from the health screening team, prompting them to pick-up their report earlier during the report collection day (report collection days were generally about 2 weeks after the health screening day) and informing them of the benefits of the study. Also, eligible individuals received a reminder phone call from NUS or KTPH staff one day prior to the report collection if this was logistically feasible. During this phone call, eligible individuals had the opportunity to ask questions about the content of the study. During the report collection day, a colored sticker was placed on the report envelope of people who were assessed as eligible by the health screening team. Eligible people were then directed to the PPT booth after collecting their reports and attending the subsequent health talks. The NUS study team then explained the study in detail, took their written informed consent and enrolled them into the study.

### 2.8. Participant Timeline

Figure 1 illustrates the participant flow and includes the time schedule of enrolment, intervention components, assessments and visits for participants.

### 2.9. Assignment of Interventions

Participants were randomized into one of the two groups based on computer-generated random numbers using Stata statistical software version 12 [31]. Block sizes were generated randomly using a minimum block size of four and a maximum block size of ten. The group assignments were handed to a separate study team member to be placed into sequentially-numbered opaque envelopes and sealed. The envelopes had the participant ID documented on the outside according to the randomization lists and a slip of paper stating ‘intervention’ or ‘control’ was placed in each envelope. The envelopes were opened by the study team member who would perform the park prescription counselling component of the intervention after confirmation of eligibility, provision of informed consent and completion of the baseline assessment in the presence of the study participants, which ensured allocation concealment. Due to the nature of the intervention and the logistics of the study, participants and research staff were subsequently not blinded to the group allocation. 

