### 2.10. Data Collection and Analysis

#### 2.10.1. Data Collection

Table 2 summarizes data collection measures and instruments at each of the three measurement time points. The types of measures are also described in detail under Section 2.5 Outcomes and this section provides information on the procedures used to ensure quality of data collection and completeness of follow-up.

At baseline, secondary outcome measures of physical health including blood chemistry (blood lipids, fasting blood glucose), blood pressure (systolic and diastolic) and anthropometry (height and weight) had been collected prior to enrolment in the trial as part of existing health screenings or as part of data collection for the existing NUS cohort study. The data at these health screenings are collected by nurses who are trained in standard procedures for collecting the anthropometric data accurately and reliably and taking blood safely. The questionnaire, which combined items from several validated questionnaires, was piloted with a small sample who were of the same age range as study participants. Pilot participants were from the National University Hospital clinics. The pilot was used to see that the time to completion was acceptable and all questions were understood. Staff were also instructed to check for missing data and plausibility. To increase participant retention, participants’ contact details were collected at baseline for follow-up.

At the three-month follow-up, self-administered questionnaires were mailed to participants for completion with a stamped, addressed return envelope as well as a letter thanking them for their participation and encouraging them to return the questionnaire within one week. If the surveys were not returned, participants received reminder text messages and if necessary follow-up phone calls. Participants who did not complete the survey at three months were still followed up at six months.

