At six-month follow-up only, participants received a letter which invited them to attend a follow-up health screening at KTPH. In most cases the letter, including the questionnaire, accelerometer and instructions for wearing it were hand delivered to participants near the end of the program at their homes so an explanation on wearing the accelerometer could be provided. The accelerometer was worn on the participant’s wrist for seven days. The instructions explained that it must be worn on the wrist of the non-dominant hand at all times for seven consecutive days as soon as possible after receiving it. To increase the chances of collecting complete data for at least four valid days for each participant, a trained study team member collected the accelerometer and downloaded the data to a laptop with the full ActiLife software installed. The study team member checked the number of complete days of data provided and if there were less than four they asked the participant to wear another accelerometer for another seven days.

During the scheduled visit at KTPH, participants answered the questionnaire (if it had not been completed in advance), returned the accelerometer and underwent a health screening. For participants in the intervention arm, the questionnaire also assessed satisfaction with the phone counselling component of the program as well as the program overall. To maximize attendance at the six-month follow-up health screening session participants were reminded that they would receive their final $30 cash incentive at this session.

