#### 2.10.2. Data Management

Hard copies of the baseline and follow-up questionnaires are stored in a locked cabinet in the Principal Investigator’s (PI’s) office at the Saw Swee Hock School of Public Health (SSHSPH), NUS. All participants were given a unique identification number. This identification number was used on all measurements collected. These were only accessible to members of the research team who needed to access them. All data were de-identified using the unique identification number. 

The data from the questionnaires will be entered into a spreadsheet by trained research staff. This data will only be accessible to members of the research team who require access to it. All datasets will be de-identified and no names or contact information will be part of the datasets. A master key, or ‘participant identity log’ will only include participant names, contact information and identification numbers. This master key, or ‘participant identity log’ will be kept separately from the main research data in a password-protected document. Datasets will be stored on a secure centralized computer within SSHSPH, which is password-protected. Additional backup files will be on external hard drive disks. All data sets will be under password protection. All team members agree to maintain in strict confidence the names, characteristics, questionnaire scores, ratings, incidental comments, and/or other information on all subjects and/or subjects’ data they encounter. The PI will have access to the centralized computer that contains the research data. Study team members will have access to the data on their computers (which are password-protected). Research data used in publication will be kept for a minimum of 10 years before being discarded. All research-related data will be erased and mediums will be disposed of in a way that ensures that research data cannot be retrieved.

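### The protocol's reason for leaving research staff unblinded does not reach accelerometer processing or the primary analysis, where the arm can still be withheld

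*Protocol article*

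**What the plan says.** Section 2.9 (Assignment of Interventions) describes concealed allocation in sealed opaque envelopes. It adds: "The envelopes were opened by the study team member who would perform the park prescription counselling component of the intervention". It then says of the period after allocation that "participants and research staff were subsequently not blinded to the group allocation", and gives the reason as "Due to the nature of the intervention and the logistics of the study". No role is excepted, and no other section mentions a masked assessor, data processor or analyst.

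Section 2.10.1 describes the handling of the primary-outcome device at six months: "a trained study team member collected the accelerometer and downloaded the data to a laptop with the full ActiLife software installed". It continues: "The study team member checked the number of complete days of data provided and if there were less than four they asked the participant". The request was for a second week of wear.

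Section 2.10.2 says of confidentiality that "All data were de-identified using the unique identification number". The arm is not mentioned there.

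Section 2.10.3 sets out the t-test and the linear regression in the future tense and is silent on masking. The limitations in Section 4 (Discussion) cover loss to follow-up and the modest effects expected on physical health indicators. They do not mention lack of blinding.

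**The concern.** The reason in Section 2.9 has a natural limit. Participants know whether they attend weekly classes. The counsellor opens the envelope. Staff who visit homes to deliver and collect devices can hardly be kept unaware. None of this applies to someone working on stored files, or to the statistician, for whom the arm is one variable that can be held back. As worded, the sentence covers any research staff member, while its reason covers only some of them.

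The trial's main protection against the consequences of open allocation is that MVPA is recorded by a device. That protects the recording. It does not protect the later choices that turn acceleration into weekly MVPA minutes, such as intensity threshold, non-wear handling, and which days and participants count. The article may properly leave those choices to an analysis plan, and their absence is not the complaint. The point is that they should be settled by people who cannot see which choice helps which arm.

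Holding data under an ID number does not achieve this. Section 2.9 puts the participant ID on the envelope according to the randomisation lists, and Section 2.10.2 puts the participant's unique number on every measurement. The ID does not itself show the arm, but anyone with access to the list can make the link.

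**Working it through.** **Step 1. Does the stated reason cover each step?**

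| Step | Where | Status in the article | Reason in 2.9 applies? |
|---|---|---|---|
| Counselling, classes | 2.4.1, 2.9 | done | yes |
| Device delivery, collection, download, day count, repeat-wear request | 2.10.1 | done | yes: staff deal with participants directly |
| Conversion of files to MVPA minutes; final valid-day and exclusion decisions | not described | not described as done | no |
| Primary analysis | 2.10.3 | future tense | no |

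The gap lies in the last two rows.

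**Step 2. Effect on sample size.** The article gives no figure for blinding. Its sample size (Section 2.6) rests on a difference of 30 and an SD of 60 min/week, two-sided 5%, 80% power. The normal approximation gives n = 2 × (1.96 + 0.842)² × 60² / 30² = 62.8, so 63 per group. The two-sample t-test gives 63.77, so 64, as stated. Then 64 / 0.80 = 80 per group, 160 in total, also as stated. Masking alters none of these inputs.

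**Step 3. Illustration of what is at stake.** All inputs here are assumptions, since the documents supply none. Suppose there is no true effect, k processing definitions are available, their test statistics Z₁,…,Z_k are standard normal with common correlation r, and the definition most favourable to the intervention is used. With φ and Φ the standard normal density and distribution function:

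P(false claim of benefit) = P(max Z > 1.96) = 1 − ∫ φ(u) · Φ((1.96 − √r·u)/√(1−r))^k du

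P(false claim of harm) = P(max Z < −1.96), from the same integral with −1.96 in place of 1.96.

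By numerical integration:

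| k | r | False benefit | False harm | Two-sided total |
|---|---|---|---|---|
| 1 | – | 2.5% | 2.5% | 5.0% |
| 2 | 0.9 | 3.5% | 1.5% | 5.0% |
| 2 | 0.8 | 3.9% | 1.1% | 5.0% |
| 2 | 0.6 | 4.4% | 0.6% | 5.0% |
| 4 | 0.9 | 4.7% | 0.9% | 5.6% |
| 4 | 0.8 | 5.7% | 0.5% | 6.2% |
| 4 | 0.6 | 7.2% | 0.2% | 7.4% |

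For k = 2 the total stays at 5% because the gain on one side equals the loss on the other. The harm is therefore best read from the false-benefit column. If the definition is fixed while the arm is withheld, the choice cannot depend on the arm and the k = 1 row applies.

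**The case against.** The strongest reply is that the sentence in Section 2.9 is a past-tense account of trial conduct, under a heading about assignment. It does not say that the person who derives MVPA or runs the analysis knows the arm, and masking of the analyst may well be in an analysis plan that is not shown. This stands. A reader might infer that every member of staff, including the statistician, was unblinded; the article does not say so. What remains is that the sentence has no exception and its reason does not fit the later steps.

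A reader might also infer that the valid-day check let staff favour one arm. The article does not support that. The repeat-wear request has a fixed trigger of fewer than four complete days, and differential effort in pursuing it would be speculation. That fieldwork is also described as done, so no change to it is proposed.

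The instruction that "Staff were also instructed to check for missing data and plausibility" is tempting as further evidence. However, it stands in the baseline paragraph next to the questionnaire pilot, and envelopes were opened only after the baseline assessment. It says nothing about accelerometer data. Some follow-up questionnaire items went only to the intervention arm, but questionnaires do not supply the primary outcome.

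Finally, derivation of MVPA from raw wrist acceleration is an inference. The article states its acceleration metric (ENMO) only for total activity volume (Table 2, note a).

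**Conclusion.** The point holds in a limited form. Section 2.9 states non-blinding of research staff without exception. Its reason accounts for participants and for delivery and field staff, but not for file processing or the primary analysis. Those steps are not described as complete, and withholding the arm there is a cheap protection for the primary outcome of an open trial.

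No bias has been shown, and its size cannot be taken from the documents. The only magnitude offered is conditional: with two to four candidate definitions correlated 0.9 to 0.6, free choice with the arm known would raise false claims of benefit from 2.5% to between 3.5% and 7.2%. A reader might put the damage higher, at 7.0–8.7% (k = 2) or 9.4–14.4% (k = 4) two-sided. Those figures count picking whichever definition is significant in either direction, which is not the harm at issue when staff would favour the intervention.

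If processing and analysis are in fact masked, the defect is only that Section 2.9 is worded too broadly.

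**What to change.** - **Section 2.9:** keep the statement that participants and delivery and field staff were unblinded, since it reports what happened, and limit it to them.
- **Sections 2.10.2 and 2.10.3:** add that accelerometer files are re-coded with a number unrelated to the allocation list; that MVPA derivation and the valid-day and exclusion decisions are fixed with the arm code withheld; and that the primary analysis is run on arms labelled A and B until data and code are locked.
- **Section 4:** list the unblinded field staff as a limitation.

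If any of these steps has already been carried out with the arm known, say so instead.

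The cost is a small re-labelling task and one variable held back by someone outside the processing and analysis. It is low rather than nil. The sample size and the completed fieldwork are unaffected.

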### 2.10. Data Collection and Analysis

#### 2.10.1. Data Collection

Table 2 summarizes data collection measures and instruments at each of the three measurement time points. The types of measures are also described in detail under Section 2.5 Outcomes and this section provides information on the procedures used to ensure quality of data collection and completeness of follow-up.

At baseline, secondary outcome measures of physical health including blood chemistry (blood lipids, fasting blood glucose), blood pressure (systolic and diastolic) and anthropometry (height and weight) had been collected prior to enrolment in the trial as part of existing health screenings or as part of data collection for the existing NUS cohort study. The data at these health screenings are collected by nurses who are trained in standard procedures for collecting the anthropometric data accurately and reliably and taking blood safely. The questionnaire, which combined items from several validated questionnaires, was piloted with a small sample who were of the same age range as study participants. Pilot participants were from the National University Hospital clinics. The pilot was used to see that the time to completion was acceptable and all questions were understood. Staff were also instructed to check for missing data and plausibility. To increase participant retention, participants’ contact details were collected at baseline for follow-up.

At the three-month follow-up, self-administered questionnaires were mailed to participants for completion with a stamped, addressed return envelope as well as a letter thanking them for their participation and encouraging them to return the questionnaire within one week. If the surveys were not returned, participants received reminder text messages and if necessary follow-up phone calls. Participants who did not complete the survey at three months were still followed up at six months.

At six-month follow-up only, participants received a letter which invited them to attend a follow-up health screening at KTPH. In most cases the letter, including the questionnaire, accelerometer and instructions for wearing it were hand delivered to participants near the end of the program at their homes so an explanation on wearing the accelerometer could be provided. The accelerometer was worn on the participant’s wrist for seven days. The instructions explained that it must be worn on the wrist of the non-dominant hand at all times for seven consecutive days as soon as possible after receiving it. To increase the chances of collecting complete data for at least four valid days for each participant, a trained study team member collected the accelerometer and downloaded the data to a laptop with the full ActiLife software installed. The study team member checked the number of complete days of data provided and if there were less than four they asked the participant to wear another accelerometer for another seven days.

During the scheduled visit at KTPH, participants answered the questionnaire (if it had not been completed in advance), returned the accelerometer and underwent a health screening. For participants in the intervention arm, the questionnaire also assessed satisfaction with the phone counselling component of the program as well as the program overall. To maximize attendance at the six-month follow-up health screening session participants were reminded that they would receive their final $30 cash incentive at this session.

#### 2.10.2. Data Management

Hard copies of the baseline and follow-up questionnaires are stored in a locked cabinet in the Principal Investigator’s (PI’s) office at the Saw Swee Hock School of Public Health (SSHSPH), NUS. All participants were given a unique identification number. This identification number was used on all measurements collected. These were only accessible to members of the research team who needed to access them. All data were de-identified using the unique identification number. 

The data from the questionnaires will be entered into a spreadsheet by trained research staff. This data will only be accessible to members of the research team who require access to it. All datasets will be de-identified and no names or contact information will be part of the datasets. A master key, or ‘participant identity log’ will only include participant names, contact information and identification numbers. This master key, or ‘participant identity log’ will be kept separately from the main research data in a password-protected document. Datasets will be stored on a secure centralized computer within SSHSPH, which is password-protected. Additional backup files will be on external hard drive disks. All data sets will be under password protection. All team members agree to maintain in strict confidence the names, characteristics, questionnaire scores, ratings, incidental comments, and/or other information on all subjects and/or subjects’ data they encounter. The PI will have access to the centralized computer that contains the research data. Study team members will have access to the data on their computers (which are password-protected). Research data used in publication will be kept for a minimum of 10 years before being discarded. All research-related data will be erased and mediums will be disposed of in a way that ensures that research data cannot be retrieved.

